## Abstract

**Background:**

Mobile health, the use of mobile technology in delivering health care, has been found to be effective in changing health behaviors, including improving breastfeeding practices in postpartum women. With the widespread use of smartphones and instant messaging apps in Hong Kong, instant messaging groups could be a useful channel for delivering breastfeeding peer support.

**Objective:**

The aim of this paper is to study the feasibility and acceptability of an online instant messaging peer support group by trained peer counselors on improving breastfeeding outcome in primiparous women in Hong Kong.

**Methods:**

A two-arm, assessor-blind, randomized controlled feasibility study will be conducted on 40 primiparous women with the intention to breastfeed. Participants are recruited from the antenatal obstetrics and gynecology clinic of a public hospital in Hong Kong and randomly assigned at a 1:1 ratio to either intervention or control group. The intervention group receives peer support in an online instant messaging group with trained peer counselors on top of standard care, whereas the control group receives standard care. Breastfeeding outcome will be assessed for 6 months post partum or until weaned. The breastfeeding status, the proportion and duration of exclusive and any breastfeeding in each group, and the self-efficacy and attitude of participants will be assessed. The feasibility and acceptability of the study would also be assessed in preparation for a full randomized controlled trial.

**Results:**

This study (protocol version 1 dated January 5, 2021) has been reviewed and approved by the institutional review board of the University of Hong Kong, Hospital Authority Hong Kong West Cluster (reference UW 21-039), on January 26, 2021. Data collection is ongoing and expected to be completed in December 2021. The findings will be updated on clinical trial registry and disseminated in peer-reviewed journals.

**Conclusions:**

This study aims to assess the feasibility and effectiveness of an online instant messaging peer support group in improving the breastfeeding outcome of primiparous women in Hong Kong. Its findings could inform the feasibility of a full-scale trial with this intervention design.

**Trial Registration:**

ClinicalTrials.gov NCT04826796; https://clinicaltrials.gov/ct2/show/NCT04826796

**International Registered Report Identifier (IRRID):**

DERR1-10.2196/32338

## Introduction

Mobile health (mHealth) is the delivery of medical and public health practices using mobile devices [1]. With the advances and increasing ubiquity in mobile technologies, there is an increase in the use of mHealth interventions for promoting healthy infant feeding practices and breastfeeding. A recent meta-analysis has reported that mHealth significantly improved exclusive breastfeeding initiation, breastfeeding attitude, and knowledge [2]. However, the effectiveness of the more interactive and adaptive platforms, such as smartphone apps and social networking tools, in improving breastfeeding outcomes remains understudied.

Smartphones and social networking apps have emerged in recent years as the new tool for information acquisition and exchanges. In 2019, the number of smartphone users in Hong Kong was estimated to reach 6.5 million. It is predicted that 93% of the population in Hong Kong will be smartphone users by 2025 [3]. Previous studies have found the use of these online discussion and social networking platforms to be an acceptable, affordable, and accessible method for a range of health promotion intervention, including promoting physical activities [4], healthy diet [5], smoking cessation [6], and reducing alcohol use [7]. As these communication tools allow for more personalized and instant response without time and location limitations, interventions delivered through online social networking platforms tend to have a high uptake. These platforms could be a promising tool for breastfeeding promotion. A recent integrated review has found that women tend to seek online breastfeeding support if they were isolated or do not receive sufficient professional support, and that online support could be an accessible and easily available channel for them to learn from others’ experience [8]. Nevertheless, most studies on the topic to date have focused on the qualitative aspects of the online support experience [8], and there remains a lack of intervention studies on online peer support intervention. Moreover, existing data on whether online breastfeeding peer support could help improve breastfeeding outcome remain scarce and inconclusive [8].

According to the most recent survey, more than 87.5% of women initiated breastfeeding in Hong Kong in 2018 [9]. However, half of the breastfeeding women have never exclusively breastfed their babies [9]. The exclusive breastfeeding rate tailed off during the first 2 months and dropped to 26.3% at 6 months [9]. Considering the importance of exclusive breastfeeding in the first 6 months, this low exclusive breastfeeding rate is of public health concern. While practices vary, many women in Hong Kong continued to adopt postnatal rituals that Chinese women adhere to in the first month post partum, such as staying at home, eating prescribed foods (eg, chicken and Chinese ginger), and avoiding bathing or washing their hair. This would consequently mean that Chinese women would stay homebound for 1 month after giving birth and often follow specific restrictions on their diets and activities. The existing antenatal and postnatal breastfeeding support is mainly provided by hospitals and maternal and child health centers, which due to the pandemic, have been further limited. Postpartum women in Hong Kong, thus, may face additional challenges in seeking timely breastfeeding support. Unresolved problems and inadequate support are risk factors for women to cease exclusive breastfeeding early [10,11]. There is a need for innovative approaches to engage and support breastfeeding women in the first 6 months after childbirth.

Thus, a randomized controlled feasibility study is proposed with the aim to examine the practicality and feasibility of supporting Chinese breastfeeding mothers in Hong Kong. In a previous study conducted in Hong Kong, it is suggested that peer support delivered via instant text messages could be a viable way of promoting breastfeeding [12]. The instant messaging smartphone app, WhatsApp (WhatsApp Inc), is one of the most used social networking platforms in Hong Kong [13]. It is a free all-in-one app for sending text and voice messages, multimedia contents, and video calls. The proposed intervention aims to address an important service gap in Hong Kong to promote and sustain exclusive breastfeeding. While WhatsApp has been used as a tool to deliver professional breastfeeding support in countries such as Turkey [14], this will be the first WhatsApp breastfeeding support intervention provided by trained peer supporters in Hong Kong. However, there might be potential barriers to a successful implementation of the intervention and evaluation of its effectiveness. Therefore, a feasibility pilot study is proposed to identify if a WhatsApp online group on breastfeeding by peer counselors, delivered through instant messaging support and designed to improve breastfeeding outcomes, is feasible and acceptable.

This trial was registered on ClinicalTrials.gov (NCT04826796) on April 1, 2021.

## Methods

### Study Aim

The main objective of the study is to determine the feasibility and acceptability of an online messaging support group hosted by trained peer counselors on breastfeeding outcome in women with intention to breastfeed in Hong Kong over a 6-month period.

### Trial Design

This trial adopts a randomized controlled superiority design with 2 parallel groups and a primary end point of cessation of breastfeeding in the first 6 months post partum. Participants will be randomly allocated to the intervention or control group on a 1:1 ratio.

### Study Setting

Participant recruitment will be conducted at the obstetrics and gynecology outpatient clinic at a public hospital in Hong Kong serving an urban population.

### Sample Size

The sample size of the trial is 40 participants, with 20 participants in each arm. As this is a feasibility and pilot study that aims to gauge the rate of recruitment, adherence, and retention levels, as well as to identify unanticipated issues of the trial design, this recommended sample size for feasibility and pilot study is used [15]. Recruitment will continue until target sample size is reached.

### Inclusion and Exclusion Criteria

To be eligible for inclusion in the study, participants must (1) be primiparous, (2) intend to breastfeed, (3) have a singleton pregnancy, (4) have term infant (37-42 weeks gestational), (5) be Cantonese speakers, (6) reside in Hong Kong, and (7) have no serious medical or obstetrical complications.

Individuals will be excluded from the study if they fail to meet the inclusion criteria or if their newborn (1) are <37 week gestation; (2) have an Apgar score <8 at 5 minutes; (3) have a birthweight <2500 grams; (4) have any severe medical conditions or congenital malformations; (5) are placed in the special care baby unit for more than 48 hours after birth; or (6) are placed in the neonatal intensive care unit at any time after birth. Participants who are, due to mental or physical reasons, unable to provide written informed consent are also excluded from the study.

### Recruitment, Randomization, and Allocation of Intervention

Recruitment will be conducted at the obstetrics and gynecology outpatient antenatal clinics in a public hospital in Hong Kong. Research assistants will have obtained written informed consent from participants. All eligible participants who consented to participate will be randomized. They will be randomly assigned to either the intervention or control group at a 1:1 ratio. The randomization sequence was computer generated using STATA (Stata Corp) with simple randomization by a researcher prior to study recruitment. The sequence will be concealed in a password-encoded excel file, which will not be assessed by nor disclosed to a second researcher responsible for participant recruitment and data collection. After the participants are recruited and the baseline assessments have been completed, a third researcher with access to the randomized sequence will notify the participants of their group assignment.

Due to the nature of the study, a single-blind design is used. The participants will be notified of their group assignment after the completion of baseline assessment. The researcher responsible for study recruitment and assessments will be blinded to group allocation.

### Intervention

The participant timeline in the study is outlined in Table 1. The control group will continue to receive standard care, whereas the intervention group will, in addition to standard care, be included in a breastfeeding support group on a popular online messaging mobile app, WhatsApp (“WhatsApp group”), with trained peer counselors. The participants will be notified before they were added to the group and will receive a standard welcome message in the group afterward. The message will introduce the peer counselors and encourage participants to raise any question or concern they may have. Peer counselors will send prompts asking for questions or send information related to breastfeeding every week for 6 months. No harm to the participants is anticipated. The participants could leave the WhatsApp group on their own if they wish to discontinue the intervention. The participants are permitted to receive other professional breastfeeding support.

**Table 1 table1:** Participant timeline in the WhatsApp breastfeeding peer support study.

Point of contact		Study Period					
		Enrollment	Allocation	Postallocation			
		Study entry	Allocation	1 month post partum	2 months post partum	3 months post partum	6 months post partum
**Enrollment**							
	Eligibility screen	✓					
	Informed consent	✓					
	Allocation		✓				
**Interventions**							
	Control group			Standard care			
	Intervention group			WhatsApp peer support group and standard care			
**Assessments**							
	Demographics	✓					
	Infant feeding status			✓	✓	✓	✓
	Breastfeeding self-efficacy	✓			✓		
	Breastfeeding attitude	✓			✓		

In this trial, the WhatsApp group includes 4 trained peer counselors, 1 of whom is an experienced trainer, and all participants are allocated to the intervention group. The trained peer counselors are all women living in Hong Kong with at least 4 months of breastfeeding experience. All of them have been trained under the Breastfeeding Peer Support Scheme organized by Natural Parenting Network and have received at least 16 hours of training, attended 2 practicums, and passed a standardized assessment. The training program covered topics including (1) why breastfeeding is important, (2) how to assure good start of breastfeeding, (3) how to help mother breastfeeding, (4) communication skills, (5) common breastfeeding problems, (6) diet and hygiene, (7) maternal illness and needs, and (8) local support and role of peer counselors. The peer counselors were assessed by their trainers after completing the training program.

### Outcomes

The feasibility of the study will be examined based on the proportion of participants agreed to participate in the study and the acceptance of women to be randomized; completion of the intervention and follow-up at 6 months post partum will also be measured. Data on the number of women approached and screened and the reasons for rejection or exclusion will be collected. In addition, the women’s views on the intervention, including strengths, weaknesses, and room for improvements, will be assessed at each follow-up time points. The reason for dropping out of intervention would be recorded. Women in the intervention group will also be invited to a qualitative interview assessing their views on the intervention at the end of the study.

In terms of intervention efficacy, the primary outcome of the study is the infant feeding status. We will collect data on the participants’ infant feeding status at 1, 2, 4, and 6 months post partum. The infant feeding status will be classified according to the World Health Organization definitions in the 24 hours prior to each data collection period [16]. We will compare the proportion of any and exclusive breastfeeding among participants in the intervention and control groups. The secondary outcomes are the breastfeeding self-efficacy and attitude of the participants. Breastfeeding self-efficacy will be measured using the Hong Kong Chinese version of the Breastfeeding Self-Efficacy Scale-Short Form (BSES-SF) [17]. BSES-SF is a 14-item scale with total score ranging from 14 to 70, with a higher score indicating higher breastfeeding self-efficacy [18]. Attitude toward breastfeeding will be measured using the Chinese version of the 17-item Iowa Infant Feeding Attitude Scale (IIFAS) [19]. The total score ranges from 17 to 85, with a higher score indicating a more favorable attitude toward breastfeeding [20]. The breastfeeding self-efficacy and attitude of participants will be measured at study entry and 2 months post partum. All participants will be followed for 6 months post partum or until weaned.

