### Data Collection Method

Demographic information and breastfeeding self-efficacy and attitude will be collected from the participants at study entry. The participants will be asked to complete the questionnaires after providing informed consent to participate. Demographic information such as age, educational level, household income, intention to exclusively breastfeed, and intended duration of any and exclusive breastfeeding, whether they were breastfed as a child, and whether they know someone with breastfeeding experience, were collected. Maternal and birth data will be collected by the research assistant from the participants’ medical records. Follow-up assessments will be conducted via telephone interviews at 1, 2, 4, and 6 months post partum by the research assistant. To promote retention, the participants will be asked their preferred time of contact for the phone interviews. Infant feeding status will be assessed at all 4 follow-up time points, whereas the breastfeeding self-efficacy and attitude will be assessed at 2 months post partum. Any professional breastfeeding support received will also be recorded.

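### Asking for views on the intervention at every follow-up can unmask the blinded telephone interviewer from month 1, and the article describes no separation of the two tasks

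*Protocol article*

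**What the plan says.** All references are to the protocol article.

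- **Abstract, Methods:** "A two-arm, assessor-blind, randomized controlled feasibility study will be conducted on 40 primiparous women with the intention to breastfeed".
- **Recruitment, Randomization, and Allocation of Intervention:** "The researcher responsible for study recruitment and assessments will be blinded to group allocation". The same section makes this person responsible for data collection as well as recruitment. Mothers are not masked: "The participants will be notified of their group assignment after the completion of baseline assessment". A third researcher holds the sequence and gives out the assignments.
- **Intervention:** "The control group will continue to receive standard care". Only the other arm joins the WhatsApp group.
- **Outcomes:** for efficacy, "the primary outcome of the study is the infant feeding status". Women's "views on the intervention, including strengths, weaknesses, and room for improvements, will be assessed at each follow-up time points", and reasons for dropping out of the intervention are recorded. A qualitative interview with intervention women at the end of the study is listed separately.
- **Data Collection Method:** "Follow-up assessments will be conducted via telephone interviews at 1, 2, 4, and 6 months post partum by the research assistant", and "Infant feeding status will be assessed at all 4 follow-up time points". Self-efficacy and attitude are measured after baseline only at 2 months.

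**The concern.** A question about the strengths and weaknesses of the WhatsApp group can be answered in substance only by a woman who is in it. An interviewer who asks it, or hears the answer, learns that she is in the intervention arm. A woman with nothing to comment on is identified as a control. If the blinded assessor handles this item at month 1, that person knows the allocation before the later calls.

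What is at stake is the efficacy comparison. Feeding status is obtained orally, from mothers who know their arm, and the interviewer's probing and coding help decide whether a woman counts as exclusively breastfeeding. Masking the interviewer is a safeguard against that probing and coding differing by arm. If it is lost, the trial would be reported as assessor-blind when most of its feeding data might not have been collected that way. A full-scale trial modelled on this one could inherit the same procedure.

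**Working it through.** The article gives no figure of its own to reproduce here. The check is a cross-reading, followed by a count.

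**1. Who makes the calls?** The recruitment section blinds the researcher who recruits, collects data and assesses. It also has research assistants obtaining consent. Data Collection Method gives the follow-up interviews to the research assistant. On the natural reading, the blinded assessor and the telephone interviewer are the same role.

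**2. When are views collected?** At each follow-up time point, that is, at the same points as the calls. They cannot be explained as the end-of-study qualitative interview, which is listed in addition.

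**3. Does the item reveal allocation?** If every woman is asked, the content of the answer separates the arms. If only intervention women are asked, whoever asks must know whom to ask. Either way, the person handling the item learns the arm.

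**4. Is any separation described?** No. The article mentions no second interviewer, self-completed form or question order for these items. The third researcher knows the allocation, but that person's only stated tasks concern the sequence and the notification of assignment.

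**5. How many assessments could be exposed?** Inputs: 40 women, 20 per arm (Sample Size); 4 calls per woman (Data Collection Method). Table 1 shows the third follow-up at 3 months instead of 4. The count is the same on either schedule.

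| Quantity | Calculation | Result |
|---|---|---|
| Maximum feeding-status assessments | 40 × 4 | 160 |
| Month-1 assessments | 40 × 1 | 40 |
| Assessments after month 1 | 40 × 3 | 120 |
| Share exposed if feeding status is asked first | 120 / 160 | 75% |
| Share exposed if views are asked first | 160 / 160 | 100% |
| Month-2 administrations of each scale | 40 × 1 | 40 (all of the post-baseline scores) |

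The 75% row assumes that the views are collected in the assessor's own call from month 1, that the same assistant calls each woman throughout, that the allocation is not known before the month-1 feeding answer is recorded, and that all 40 women complete all four calls. Follow-up ends at weaning if that comes before 6 months, so 160 and 120 are both ceilings.

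**6. How sensitive is the comparison?** With 20 women per arm, one woman classified differently moves that arm's proportion by 1 / 20 = 5 percentage points. This shows the sensitivity of the result. It is not an estimate of bias.

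**The case against.** **The article does not say that the blinded assessor asks for the views.** The sentence is in the passive and names no interviewer and no mode. The list of follow-up items under Data Collection Method does not include views, and neither do the assessment rows of Table 1. Research assistants appear in the plural elsewhere, and an unblinded third researcher already exists. A reader might infer that the assessor must ask, and so that the blinding fails. The documents support only that it can fail as written. This limit stands. It does not dispose of the point, because the sections assign follow-up assessments and data collection to the blinded role and place the views at the same time points. The conflict is between two stated procedures and is more than an omitted detail.

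**The 75% is a ceiling.** This stands, for the reasons given with the count.

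**Masking is not the only protection.** A reader might conclude that nothing else guards the outcome. That is not so: feeding status is classified by World Health Organization definitions over the preceding 24 hours, and a fixed definition with short recall narrows the room for discretion. It narrows it without replacing masking.

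**Bias has not been shown.** A reader might go on to treat any apparent benefit as interviewer bias. The documents give neither a size nor a direction for such bias. Mothers know their arm and report the outcome themselves, so reporting bias would remain even with a perfectly masked interviewer.

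**The main aim is feasibility and acceptability.** This stands, and it limits the weight of the point. The article nevertheless describes a superiority design with a breastfeeding end point and applies a 5% significance level to all tests, so the comparison between arms will be reported and read.

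**Conclusion.** The point holds as an inconsistency that should be resolved. The article claims a blinded assessor, and then schedules at every follow-up an item that discloses allocation, without saying how the two are kept apart. Unless someone else collects the views, the interviewer can learn the arm from the month-1 call. If the same assistant makes all calls and asks feeding status first, at most 120 of 160 feeding-status assessments would be unmasked, along with all post-baseline self-efficacy and attitude scores. If views come first, the month-1 feeding answers are exposed too.

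The consequence is weaker protection against interviewer probing and coding in the efficacy comparison. Recruitment, acceptance of randomization, completion and retention are unaffected. The documents do not support the stronger conclusions that blinding is certain to fail or that an observed benefit would be an artefact. This is a cheap improvement to the conduct of the trial, and no ground for setting its main aim aside.

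**What to change.** 1. Take the questions on views and on reasons for leaving the intervention out of the blinded assessor's calls. Collect them by a self-completed form or through the third researcher, who already knows the allocation. Alternatively, ask them only after the 6-month feeding data have been recorded.
2. Keep those answers away from the assessor until then. Data Management Plan has research assistants entering the data and holding access to the data set, so the answers could otherwise reveal the arm at data entry.
3. Have the assessor record feeding status and the scale scores first in each call, and open by asking the woman not to say which group she is in.
4. Log every unblinding with its time point, and report the number by arm.
5. If the views must stay in the assessor's calls, withdraw the assessor-blind description and say that the interviewer may know the allocation after month 1.

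If the full protocol already assigns the views to someone else, one sentence in the article settles the matter.

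The cost is a possibly lower response to a form than to a telephone question, or later and less fresh answers if the views are deferred. There is also some added work for the third researcher, whose capacity for repeated contacts the article does not document. The repair restores interviewer masking only; mothers' knowledge of their own arm remains a limitation to state when the results are reported.
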